### Recruitment {15}

Potential SMART participants are screened using a two-step process. First, a weekly patient list is extracted from the EMR, cleaned in excel, and imported into the study’s REDCap database. A member of the study team will review each patient’s REDCap record and assess preliminary eligibility based on exclusionary medical conditions (see above for full list of exclusion criteria), living status, and the date and value of the most recent HbAlc level (within 90 days). Second, participants that may be eligible based on a preliminary assessment of their medical record will be contacted to complete a phone screening. During the phone screening, a member of the study team will obtain patient-reported eligibility information including race/ethnicity, confirmation of medical conditions, smartphone access, and ability to attend in-person diabetes education sessions. Participants who are eligible are invited to attend an in-person enrollment appointment. Participants who may be eligible, but do not have an HbA1c measurement within the past 90 days, will be encouraged to make an appointment with their provider to determine eligibility.

Focus group recruitment will utilize criterion sampling, using participation in the SMART study as the criterion for focus group eligibility. A total of 12 focus groups will be conducted over the course of the project. Three months after the initial SMART study recruitment, patients within each of the two initial study conditions will be randomly ordered, and a member of the study team will go down the list of randomized patients and contact each patient by phone to describe the focus group, timeline, and benefits and risks of participation. This will continue until eight patients per study condition agree to participate. Participants will be scheduled to participate in a 2-h focus group. The same recruitment strategy will be used for the final eight focus groups after rerandomization.

Center staff (e.g., clinicians, diabetes educators, community health workers) actively engaged in delivery of one of the three interventions will be invited to participant in an interview. We will seek role variability with at least one staff member from each type of role (*n* = 10). After contacting the staff member by email and confirming their interest in participating, a study team member will provide the staff person an in-depth description of the study, the timeline, and benefits and risks of participation. Eligible Center staff will be scheduled to participate in a 45-min semi-structured interview.

## Assignment of interventions: allocation

### Sequence generation {16a}

The sequence of study arm assignment will be done using a modified version of the sequentially numbered, opaque sealed envelopes (SNOSE) [30]. In order to empower study participants to ensure they feel like part of the study and have a sense of autonomy, we created randomization envelopes that participants will be able to choose from. Following guidance from Doig & Simpson, we took several steps to design and create randomization allocation envelopes that will be concealed from the participant and the researcher. We developed a detailed operating procedure and provided this to a staff member who is unfamiliar with the research study. For the first randomization, the staff member printed out 150 pieces of paper that say “DSMT” and 150 pieces of paper that say “RGM”. Starting with the “RGM” paper, they folded each one and put it into a completely opaque security envelope. Each envelope was sealed and the staff member wrote their initials, in pen, on the top of the envelope seal. The same steps were repeated for the DSMT paper. Once all 300 envelopes were created, the staff member created two boxes of envelopes, stratified by recruitment site. For the first box, for patients recruited from Mount Sinai Hospital, the staff member selected 75 RGM envelopes and 75 DSMT envelopes. These were shuffled thoroughly and placed in the box marked “MSH”. For the second box, for patients recruited from Holy Cross Hospital, the staff member shuffled the remaining 75 RGM envelopes and 75 DSMT envelopes and placed them in the box marked “HCH”. These boxes and their sealed envelopes were placed in a study team member’s locked office to prepare for recruitment.

Randomization envelopes were created for the second round of randomization at 6 months following a similar protocol. In this case, the staff member printed 60 pieces of paper that say “CHW,” 60 pieces of paper that say “RGM,” 60 pieces of paper that said DSMT, and 60 pieces of paper that say “CHW + RGM.” We assumed that a certain number of participants would improve by at least one percentage point and would not be randomized. After creating the 240 envelopes, the staff member created two boxes of envelopes, stratified by the initial treatment assignment. In the first box, for participants initially assigned to DSMT, the staff member shuffled and placed the CHW and RGM envelopes in the box marked “DSMT.” In the second box, for participants initially assigned to RGM, the staff member shuffled and placed the remaining DSMT and CHW + RGM envelopes in the box marked “RGM.”

### Concealment mechanism {16b}

Once the participant completes the intake and randomization, the research *staff member* will assign a participant identification number to the participant. The first number is based on the recruitment site (1 = Mount Sinai Hospital; 2 = Holy Cross Hospital). The second and third identification digits are based on the initial study arm (77 = RGM group; 88 = DSMT group). The last three digits are based on the order in which they enroll in the study, consecutively beginning with 001. This identification number will be documented on the intake form and in REDCap.

### Implementation {16c}

The two research staff involved in the recruitment will have no involvement in the allocation of participants to the interventions. The participant will select an envelope at random, and once selected, that will be the final envelope. The research staff member will document the assignment in REDCap.

## Assignment of interventions: blinding

### Who will be blinded {17a}

Only the statistician will be blinded to the intervention assignments. They will receive a de-identified dataset that will list a unique identifier other than the one noted above since the identifier above includes information related to the study arm. The dataset will include a value indicating which study arm(s) participants have been assigned to at each randomization point, but the statistician will be unaware of how the code corresponds to study arms.

### Procedure for unblinding if needed {17b}

The participants and research team located at Sinai Chicago will not be blinded to the study conditions. Only the statistician, an independent consultant, will be blinded to the study conditions. The research team at Sinai Chicago will have a matrix that links participant identifiers to the codes provided to the statistician.

## Data collection and management

### Plans for assessment and collection of outcomes {18a}

#### Intervention outcome measure

The primary outcome of our study is change in HbA1c which will be calculated as three measures. We will collect HbA1c at baseline (no more than 90 days prior to patient intake), 6-month follow-up, and 12-month study end point. First, we will use change in HbA1c as the tailoring variable for our SMART. We will calculate change in HbA1c from baseline intake to 6-month follow-up. Then we will calculate change in HbA1c from baseline to 12-month follow-up and from 6-month to 12-month follow-up. Because HbA1c is an average measure of blood sugar levels of the past 3 months, clinicians often order an HbA1c test every 90 days. If it has not been at least 90 days since the patient’s last HbA1c at the 6- or 12-month follow-up, we will use an HbA1c point of care test kit (HbA1c Now by Bayer) to measure the patient’s HbA1c.

The secondary outcomes are implementation and service outcomes: fidelity, appropriateness, sustainability, and patient-centeredness. Fidelity will be measured by intervention adherence. Active RGM adherence will be measured using monthly data reports from Glooko. These will be provided at the patient level and will include number of syncs to Sinai Chicago’s EMR per month and number of blood glucose entries uploaded to Glooko per month. DSMT adherence will be calculated using attendance sheets. Participants will be adherent if they attend at least three of the four sessions. Make-up sessions will be made available to participants. Finally, adherence to the CHW intervention will include three activities: (1) completing an initial education session, (2) completing an SDoH screener, and (3) completing at least three in-person or phone touchpoints. These will be documented in the CHW tracking log and uploaded into REDCap. Appropriateness will be gathered from patient focus groups and staff interviews. Sustainability of diabetes-related learnings and self-efficacy will be measured by two validated scales: the short-form diabetes-related empowerment scale (DES-SF) and the Problem Areas in Diabetes (PAID) scale [31, 32]. Appropriateness and patient-centeredness will be collected using qualitative data. Questions to assess appropriateness will include patient and staff perceptions of appropriateness, fit and compatibility with the patient population and organizations. Questions to assess perceived patient centeredness will be related to the Institute of Medicine’s six domains of patient centeredness: (1) Respect for patients’ values, preferences, and expressed needs; (2) Coordinated and integrated; (3) Provide Information, communication, and education; (4) Ensure physical comfort; (5) Provide emotional support; (6) Involve family and friends.

### Plans to promote participant retention and complete follow-up {18b}

To minimize attrition, the research staff will call or send a text message to all study participants at least every 2 months. Those randomized to an RGM arm will receive communication from a research team member every 2 months to provide technical assistance as needed for the Glooko application. Those randomized to a DSMT arm will receive a call or text message reminder from the diabetes educator prior to each DSMT session. If a participant is unable to attend a session, the diabetes educator will offer a make-up session based on the participant’s availability. During the initial enrollment appointment, the research team will confirm or collect extensive contact information including mailing address, home and cell phone number(s), e-mail addresses, and contact information for up to three additional individuals.

### Data management {19}

Study data will be collected and managed using REDCap electronic data capture tools hosted at Sinai Chicago [33, 34]. REDCap (Research Electronic Data Capture) is a secure, web-based software platform designed to support data capture for research studies, providing (1) an intuitive interface for validated data capture; (2) audit trails for tracking data manipulation and export procedures; (3) automated export procedures for seamless data downloads to common statistical packages; and (4) procedures for data integration and interoperability with external sources. Participant data will be entered directly into the study’s REDCap database by a study team member or collected on paper and entered into REDCap by a study team member within one business day. Only study team members will have access to the REDCap database. Randomly selected data collected on paper and later entered into REDCap will be periodically reviewed to ensure data quality. Paper copies of data collection forms, signed informed consent forms, and signed HIPAA authorization forms will be stored in a locked drawer at the study site. Any exports of study data from REDCap, audio recordings, notes (Word documents) and transcripts (Word documents), will all be saved on a secure study site server and only study team members will have access to the folder storing all materials. All paper files will be stored until 5 years after study completion and will then be destroyed. Electronic data will be destroyed or fully de-identified 5 years after study completion.

### Confidentiality {27}

Procedures are in place to ensure confidentiality and provide full informed consent. The consent form and information provided to the participant will have a contact phone number to call if they have questions or concerns about any aspect of the study. The following policies and procedures will be adopted to maintain privacy and confidentiality:Data will be collected and analyzed by research staff only, password protected and housed in a secure folder on a secure server, or in a secure REDCap database, only accessible to study team members.All study staff will receive training on maintaining the privacy and confidentiality of individual information, including HIPAA training.The participants’ records will be maintained in a password-protected project database until 5 years after study completion and will then be destroyed or fully de-identified.

All paper study files, including data collection forms, signed consent forms, and signed HIPAA forms will be stored until 5 years after study completion and will then be destroyed. Electronic data files will be destroyed or fully de-identified 5 years after study completion.

### Plans for collection, laboratory evaluation, and storage of biological specimens for genetic or molecular analysis in this trial/future use {33}

We will not be collecting or storing biological specimens for future use. All lab information comes from HbA1c results ordered by a provider for standard of care. During the point of care testing, no biological specimens are being stored. Once the point of care testing is complete and resulted, information will be documented in the medical record and the test will be discarded.

## Statistical methods

### Statistical methods for primary and secondary outcomes {20a}

In our quantitative analysis, we will employ descriptive statistics to provide a comprehensive overview of our data, calculating frequencies and percentages for categorical variables, and means with standard deviations or medians with interquartile ranges for continuous variables, paying special attention to any outliers.

#### Primary outcomes

To optimize the adaptive intervention and understand the causal effects of each proposed sequence, we will employ a SMART design. This design is particularly advantageous for chronic diseases like diabetes, where there is significant heterogeneity in response to treatment. The SMART design allows for re-randomization based on a tailoring variable, which in our study is the change in HbA1c at 6 months, enabling patients to receive an adaptive intervention that is most suited to their needs. To address potential imbalances in randomization, we will use stratified and block randomization techniques.

For primary analysis, we will employ linear regression models adjusting for baseline characteristics utilizing type III sum of squares to account for these discrepancies. Sensitivity analyses will include inverse probability weighting to account for any imbalances. To assess the overall HbA1c reduction by treatment condition and the average patient percentage point reduction in HbA1c from baseline to 12 months within each of the six treatment conditions, we will utilize one-way ANOVA for mean comparisons, followed by pairwise comparisons with a Tukey post hoc test to correct for multiple comparisons. In cases of non-normal data distribution, we will opt for Kruskall-Wallis tests and a Dunn post hoc test with Hommel multiple comparison *p*-value corrections.

Linear regression will be employed to adjust for additional covariates that may confound the relationship between treatment and outcome, such as baseline characteristics with residual confounding post-randomization, and baseline and 6-month HbA1c values. We will also test for possible interactions of covariates with the treatment variable, reporting model adjusted slopes (β_ADJ_), 95% confidence intervals, model diagnostics, and goodness of fit (via R^2^).

To determine the optimal dynamic treatment regime (DTR) that maximizes the greatest benefit of percentage reduction in HbA1c at each randomization stage of the study, we will employ a Q-learning algorithm. This algorithm utilizes a Q-function *Q* (s_*i*_, *t*_*i*_) to measure the quality of assigning a treatment (*t*_*i*_) to a patient at a specific stage (*s*_*i*_), with higher reductions in HbA1c percentages yielding higher quality. Regression models will be used to estimate these Q-functions, taking into account the outcome, treatment types, and all other covariates of interest. We will assess model diagnostics and fit, and test interactions to retain significant results. With the Q-function known, the optimal DTR π^∗^(*s*_*i*_, *t*_*i*_) is determined by the treatment (*t*_*i*_) which maximizes *Q* (*s*_*i*_, *t*_*i*_) given the stage (*s*_*i*_).

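### The protocol claims block randomisation, but the procedure it describes is stratified only, and no described step ties a sealed envelope to a participant before it is opened

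*Protocol article*

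**What the plan says.** The Primary outcomes part of Statistical methods {20a} names the protection against chance imbalance: "To address potential imbalances in randomization, we will use stratified and block randomization techniques".

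Sequence generation {16a} gives the procedure. It is presented as a modified form of sequentially numbered, opaque, sealed envelopes, in which "we created randomization envelopes that participants will be able to choose from". The preparation is described step by step, and the only marking mentioned is this: "Each envelope was sealed and the staff member wrote their initials, in pen, on the top of the envelope seal". For the first randomisation "the staff member created two boxes of envelopes, stratified by recruitment site", each holding 75 RGM and 75 DSMT envelopes, shuffled. For the second there are two boxes by initial arm. One holds 60 CHW and 60 RGM envelopes, the other 60 DSMT and 60 CHW + RGM.

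Implementation {16c} sets the draw rule: "The participant will select an envelope at random, and once selected, that will be the final envelope". Staff then enter the assignment in REDCap.

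Concealment mechanism {16b} covers only the study ID, which is issued at this point: "Once the participant completes the intake and randomization". Its digits encode site, initial arm and order of enrolment.

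**The concern.** Blocking means that allocation is forced back to balance at short, fixed intervals within each stratum. Nothing in the allocation sections does this. No block size is given, and no grouping inside a box is described. A final report that repeats the Primary outcomes sentence would describe a randomisation that did not take place.

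The second part concerns safeguards. Numbered envelopes protect allocation because they must be opened in a preset order, so a skipped or repeated envelope shows. Free choice removes that order, whether or not the envelopes carry numbers. What could replace it is a record, made while the envelope is still sealed, that this envelope belongs to this participant. None is described, and the ID that could serve is created only after the arm is known.

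Participants and the site research team are unblinded. If a second envelope were drawn, or a person left out after the arm was seen, the described records would not show which participant was involved. Both randomisations use a similar procedure.

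**Working it through.** **1. Side by side**

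| Property | Primary outcomes {20a} | Sequence generation {16a}, Implementation {16c} |
|---|---|---|
| Stratified | yes | yes: by site at stage 1, by initial arm at stage 2 |
| Blocked | yes | no block size or within-box grouping; only a fixed 1:1 content per whole box |

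A whole box could be called one block of 150 (stage 1) or 120 (stage 2). A block guarantees balance only when it is used up. Stage 1 has 2 × 150 = 300 envelopes. The recruitment target is 270, which reproduces as 216 / (1 − 0.20) = 270. At least 30 envelopes therefore stay unused, and both boxes cannot be exhausted.

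**2. Arm imbalance at stage 1**

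Inputs: 75 + 75 envelopes per site, drawn without replacement. The number in one arm after n draws is hypergeometric, and the SD of the arm difference is √[n(150 − n)/149]. At n = 135: √(135 × 15/149) = 3.69.

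| Draws at a site | SD of arm difference | P(difference of 10 or more) | Same under simple randomisation |
|---|---|---|---|
| 40 | 5.4 | 9.6% | 15.4% |
| 60 | 6.0 | 13.3% | 24.5% |
| 120 | 4.9 | 6.5% | 41.1% |
| 135 | 3.7 | 0.5% | 39.0% |

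For comparison, permuted blocks of 4 or 6 (assumed sizes; the article gives none) would never allow a difference above 2 or 3 within a stratum. Small-block balance is therefore absent part-way through enrolment, but the fixed box content pulls the final difference in.

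With 135 at each site (assumed), the overall difference among 270 has SD √(2 × 13.59) = 5.2, and at least 95% of the distribution lies within 10. The relative efficiency of a two-arm comparison is 1 − (d/n)². For d = 10 and n = 270 this is 0.9986, a loss of 0.14%. For d = 10 within one site of 135 it is 0.9945, a loss of 0.5%.

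**3. Arm imbalance at stage 2**

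Assume 135 per initial arm and 40% to 80% non-responders, giving 54 to 108 draws from 60 + 60. The SD is √[n(120 − n)/119]: 5.5 at n = 54 and 3.3 at n = 108. A difference of 10 among 68 draws (50% non-response) would cost 1 − 0.978 = 2.2% of efficiency.

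**4. Box supply**

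A site box suffices for 270 participants only if each site enrols 120 to 150. The article gives no site split. With binomial enrolment, the chance that a box runs out is 5.9% at a 50:50 split, 40% at 55:45 and 92% at 60:40 (mean shortfall about 12 at 60:40). A stage 2 box of 120 runs out if more than 120/135 = 89% of an initial arm of 135 are non-responders. The article describes no rule for an empty box.

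**5. Order of records at the first draw**

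Screening record in REDCap; consent; baseline data; participant picks an envelope; arm seen; arm-coded ID issued; assignment entered in REDCap. No described step names a particular envelope before the arm is seen. Because the ID's last digits follow enrolment order and the ID comes after the draw, a person lost between draw and ID leaves no gap in the ID series.

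**The case against.** The strongest reply is that this needs only a wording correction, because the allocation is better protected than the concern suggests. Several parts of that reply stand.

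- A reader might infer that assignments cannot be audited, or that a person who declines after seeing the arm leaves no trace. The article does not support this. Screening records, signed consent and baseline data precede the first draw. Assignments go into REDCap, which keeps audit trails. Box contents are fixed, so remaining envelopes can be counted against recorded assignments, and the seals are initialled. These records show that an assignment was made and whether totals agree. They do not show that it came from the first envelope a participant opened.
- A reader might infer that the envelopes carry no number. That rests on silence: a detailed operating procedure exists and is not shown. Free choice removes the preset order in either case.
- The article adds protections: the preparer was unfamiliar with the study, the office is locked, recruiting staff take no part in allocation, and the first pick is final. The last is a rule; no check on it is described.
- A fixed 1:1 box is a form of restricted randomisation, and the larger imbalance figures apply only part-way through enrolment.
- Small blocks at an unblinded site would make late assignments in each block easier to guess. Re-sorting the envelopes into small blocks is therefore a trade-off, and it is not recommended here.

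Condensation does not explain the contradiction itself. The article describes folding, sealing, initialling and shuffling in the past tense, so a blocking step would have belonged there. The Discussion confirms that participant selection was deliberate.

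**Conclusion.** The concern holds in a limited form and should be acted on. The statement that block randomisation will be used is contradicted by the article's own procedure, which is stratified with one fixed 1:1 box per stratum. The procedure as described also lacks a link between participant and envelope before opening, which matters because the trial is open-label at the site.

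It would be wrong to conclude that power or balance is seriously harmed. Under an even site split, the final stage 1 imbalance is small and costs well under 1% of efficiency; at stage 2, a difference of 10 at 50% non-response would cost about 2%. Box exhaustion is a contingency that depends on a site split and a non-response rate that the documents do not give. The size of any selection bias cannot be estimated from the documents, and nothing in them shows that redraws or exclusions have occurred.

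**What to change.** 1. Correct the Primary outcomes sentence: allocation was stratified (by site, then by initial arm), with a fixed 1:1 box per stratum and no smaller blocks.
2. For all remaining draws, assign an arm-neutral ID first. Write it with date and time on the sealed envelope, or log an envelope serial number against it, before opening.
3. Keep every opened envelope, and count everyone whose envelope is opened as randomised.
4. Keep spare 1:1 envelope sets for any box that may run out.

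Recruitment was expected to end in September 2024 and the second draw comes six months after enrolment, so the change mainly reaches second-stage draws. Participant choice of envelope is kept. The cost is a short procedure amendment, with a few hours of staff time.

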### Trial design {8}

This study uses a sequential, multiple assignment, randomized trial (SMART) design with approximately 270 Black/Latine patients living with diabetes recruited from two locations of a diabetes and endocrinology clinic (“the Center”) in Chicago, IL. A SMART is a type of adaptive trial that uses at least two points of randomization to build the evidence for an optimal intervention or treatment. In the IDEA study SMART, we will test three components of a team-based care model that provides diabetes care and management for patients living with diabetes and other complex health and social needs. HbA1c will serve as our pre-planned tailoring variable which will determine participant rerandomization. At 6 months, participants with an HbA1c of at least one percentage point improvement from their baseline measurement will be considered “responders”; participants with an HbA1c that has not improved by at least one percentage point from their baseline measurement will be considered “non-responders”. The study will be conducted by Sinai Urban Health Institute (SUHI), the community-engaged research institute within Sinai Chicago, a safety-net health system in Chicago, IL. See Fig. 2. IDEA Study SMART Design, for the study design. We hypothesize that path E (DSMT to CHW) will have the largest reduction in A1c compared to all other paths. DSMT provides actionable education and guidance for improving diabetes management, whereas RGM focuses on information tracking for both patients and providers. The CHW will reinforce information taught during DSMT sessions.

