### Sample size {14}

The sample size calculation, performed using G*Power (version 3.1), is based on the primary outcome of HbA1c over the 12-month study period, with the primary predictor being the six treatment conditions taken over the course of the study. The Null (H0) and Alternative (H1) Hypotheses are H0: There is no difference in the mean change in HbA1c among the six treatment groups, and H1: There is a significant difference in the mean change in HbA1c among the six treatment groups. The analysis assumes a significance level of 5%, 80% power, six treatment groups, equal group allocation, and a medium effect size of *f* = 0.25. The effect size of *f* = 0.25 was selected based on Cohen’s conventions for effect sizes in behavioral sciences, where 0.10 represents a small effect, 0.25 represents a medium effect, and 0.40 represents a large effect. A medium effect size is considered appropriate for this study, as it balances the detection of meaningful clinical differences with practical sample size considerations. Previous studies on diabetes management interventions such as DSMT and RGM have reported effect sizes in this range, indicating that a medium effect size is a reasonable expectation for interventions aimed at reducing HbA1c [13, 25].

The sample size estimation properly accounted for the multiple groups and comparisons inherent in the SMART design. Specifically, we conducted the sample size estimation for detecting a difference in HbA1c change across the six treatment groups, using an ANOVA framework, which inherently accounts for multiple comparisons. To ensure robustness and accommodate potential dropouts, we inflated the sample size by 20%. Thus, the minimum required sample size is 216 patients, and to account for an anticipated dropout rate, we aim to recruit 270 patients. This approach ensures that the study is adequately powered to detect significant differences across all treatment conditions, providing a solid basis for our subsequent analyses.

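### The six-path null, sample size, ANOVA/Tukey test and path E hypothesis compare groups sorted by 6-month HbA1c response, so the omnibus test rejects far above 5% when no intervention differs

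*Protocol article*

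**What the plan says.** **Sorting rule** (Abstract; Trial design {8}; Outcomes {12}). A participant whose HbA1c has fallen by at least one percentage point at 6 months is a responder and stays in the first arm. Everyone else is re-randomised, either to the other first-stage intervention or to CHW support. The envelope description in Sequence generation {16a} gives the second-stage options as CHW or RGM after DSMT, and DSMT or CHW + RGM after RGM.

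**Outcome** (Outcomes {12}). The primary outcome is change in HbA1c from baseline to 12 months.

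**Null and sample size** (Sample size {14}). "H0: There is no difference in the mean change in HbA1c among the six treatment groups". The calculation uses a six-group ANOVA: "The analysis assumes a significance level of 5%, 80% power, six treatment groups, equal group allocation", with f = 0.25. It concludes that "the minimum required sample size is 216 patients, and to account for an anticipated dropout rate, we aim to recruit 270 patients".

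**Analysis** (Statistical methods {20a}, Primary outcomes). The ANOVA and Tukey sentence is "we will utilize one-way ANOVA for mean comparisons, followed by pairwise comparisons with a Tukey post hoc test". The same section calls a baseline-adjusted linear regression the primary analysis, adds a regression that may adjust for 6-month HbA1c, and plans Q-learning for the optimal regime. On weighting it says "Sensitivity analyses will include inverse probability weighting to account for any imbalances". Section {20c} adds g-estimation and still lists one-way ANOVA among the models run on each imputed dataset.

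**Hypothesis** (Trial design {8}). "We hypothesize that path E (DSMT to CHW) will have the largest reduction in A1c compared to all other paths".

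**The concern.** The six conditions are not six randomised groups. Membership depends on a post-randomisation result, the 6-month change in HbA1c. The 12-month outcome is correlated with that change and is measured from the same baseline. Responder-only groups will therefore show larger 12-month falls than non-responder-only groups even if every intervention does the same thing.

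Two things are at stake. A significant omnibus test could be reported as evidence that sequences differ when it shows mainly that early responders were still better at 12 months. And path E, made up only of people who did not respond to DSMT, is asked to beat paths made up only of people who did respond. A useful CHW step could then be reported as failing the trial's stated hypothesis.

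**Working it through.** **1. The protocol's own figure.** For a one-way ANOVA with six groups, noncentrality λ = N·f². With N = 216 and f = 0.25, λ = 216 × 0.0625 = 13.5 on 5 and 210 df, and power is 81.1%. The smallest N giving 80% is 211, and the next multiple of six is 216. 216 / 0.80 = 270. Both stated numbers reproduce.

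**2. Who is in the six groups.** Fig. 2 is not shown, so the paths are rebuilt from the text: 2 first arms × responders who stay = 2 paths, and 2 first arms × 2 second-stage options = 4 paths. Of the 15 Tukey pairs:
- 2 × 4 = 8 set responders against non-responders;
- 1 compares the two responder groups;
- 4 compare non-responders across first arms;
- 2 compare the re-randomised non-responders within a first arm.

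Only the last 2 are randomised comparisons.

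**3. Size of the artefact in closed form.** The document gives no SD or correlation, so these are assumed. Let the 6- and 12-month changes be bivariate normal with common mean μ, common SD σ and correlation ρ, with no intervention effect. With z = (−1 − μ)/σ and p = Φ(z):
- responder minus non-responder gap at 12 months (in size) = ρσφ(z) / [p(1 − p)];
- spurious effect size f² = ρ²e / (1 − ρ²e), where e = φ(z)² / [p(1 − p)].

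Take μ = −0.3 and σ = 1.5. Then z = −0.467, p = 0.320, φ(z) = 0.358 and e = 0.128/0.218 = 0.588.

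| ρ | gap (points) | spurious f | λ = 216·f² | ANOVA rejection |
|---|---|---|---|---|
| 0.3 | 0.74 | 0.24 | 12.1 | 76% |
| 0.5 | 1.23 | 0.42 | 37.2 | 99.9% |
| 0.7 | 1.73 | 0.64 | 87.4 | 100% |

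Simulation agrees (74–76% at 0.3; 99.9–100% at 0.5–0.7). Even at ρ = 0.3 the artefact is about as large as the f = 0.25 the trial is powered to detect.

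**4. Range.** With σ from 1.2 to 2.0 and μ from −0.2 to −0.5, the false rejection rate is about 70–80% at ρ = 0.3 and at least 99.5% at 0.5–0.7. Responder paths look 0.6–2.3 points better.

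**5. A second model.** Here HbA1c is simulated at 0, 6 and 12 months (SD at each visit 1.5–2.0, correlations between visits 0.3–0.9, common mean change 0 to −1.0; eight scenarios). If the three correlations are equal, at r, the shared baseline makes the two changes correlate at (1 − r) / [2(1 − r)] = 0.5. False rejection rates with 216 completers:
- six-path ANOVA: 99.5–100%;
- regression adjusted for baseline HbA1c only: 37–100%;
- regression adjusted for baseline and 6-month HbA1c: 4–6%.

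**6. Path E.** In the model of step 3 (SD 1.5), a true extra 0.5-point benefit in path E puts it first among the six path means in about 14% of trials or fewer. With 1.0 point it is first in about 65%, 11% and under 1% at correlations 0.3, 0.5 and 0.7.

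**7. Regimens instead of paths.** Pool each regimen's responders (weight 1/0.5 = 2) with its non-responders (weight 1/(0.5 × 0.5) = 4). In the three-visit model with no intervention differences (SD 1.5, mean change −0.5), all four regimen means are about −0.50, so the artefact disappears. A weighted 3-df test rejected in 4.8% of null trials in one run and about 5–7% in another. With a true 0.5-point benefit, the DSMT-then-CHW regimen ranks first in 81% of trials, while path E has the largest path mean in 0%.

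**The case against.** The best defence is that the ANOVA is not the whole plan, and much of that stands.

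- **Q-learning and g-estimation** are planned for the primary outcome and suit a SMART. A reader might infer that Aim 3 goes unanswered. The document does not support that, because these methods address regimes. They do not, however, replace the stated null, carry the sample size or restate the path E hypothesis.
- **The primary label is shared** with a baseline-adjusted regression. True, but the ANOVA carries the null and the sample size, and that regression has the same fault (step 5).
- **The regression that may adjust for 6-month HbA1c** roughly holds its type I error in a linear normal model. It conditions on a post-randomisation outcome, so it does not estimate the effect of a whole sequence, and the trial is not powered on it.
- **Some Tukey pairs are valid.** A reader might infer that no planned contrast is usable. The two pairs between non-responder paths within a first arm are randomised; path E against DSMT-then-RGM is one of them. It cannot test superiority over all other paths.
- **Path E can win if the benefit is large.** A reader might infer that the hypothesis fails whatever the CHW achieves. At 1.0 point and correlation 0.3, path E ranks first in about 65% of trials. The handicap is heavy, but its weight depends on values the document does not give.
- **Weighting is not the only remedy.** It belongs to one estimator, and the methods named in {20c} are alternatives.

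**Conclusion.** The concern holds for the stated null, the basis of the sample size, the ANOVA/Tukey analysis, the baseline-adjusted regression and the path E hypothesis. With identical interventions and 216 completers, the six-path ANOVA rejects in about 70–80% of trials at a change correlation of 0.3 and at least 99.5% at 0.5–0.7, against a nominal 5%.

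These sizes rest on assumed SDs (1.2–2.0), mean changes, correlations and normality, and on the reconstruction of the six paths from the text. The direction does not: any positive correlation between the 6- and 12-month changes produces the artefact, and the shared baseline favours one. A reader might also infer that 216 and 270 are miscalculated. They are not; the arithmetic is right for a comparison that does not isolate the effect of the interventions.

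**What to change.** 1. Restate H0/H1 and the confirmatory analysis as a comparison of the four embedded regimens: DSMT then CHW if no response; DSMT then RGM if no response; RGM then DSMT if no response; RGM then CHW + RGM if no response. One suitable method is weighted-and-replicated regression of 12-month HbA1c (weight 2 for responders, 4 for non-responders, robust standard errors), adjusted for baseline HbA1c and recruitment site, with a 3-df test followed by multiplicity-adjusted pairs.
2. Restate the path E hypothesis as one about the regimen of DSMT, then CHW if no response.
3. Keep the randomised second-stage contrasts among non-responders within each first arm.
4. Report six-path means as description only.
5. Restate power in Sample size {14} for the new test at the existing 216/270.

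**Cost.** Items 1 to 4 need wording and analysis code, and no new data items. Item 5 is the real price, because the 80% power claim no longer applies. Only non-responders in a regimen receive its second step, so a CHW benefit is diluted: with 35% responders, 0.5 points becomes 0.5 × 0.65 ≈ 0.33 at regimen level. Under the assumed SD of 1.5 and before baseline adjustment, the weighted 3-df test at 216 completers has about 26–32% power for a 0.5-point CHW benefit after DSMT, and about 82–88% for 1.0 point.
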